## Methods

### Reform to the general medical services contract in England

The 2014/15 General Medical Services contract introduced a requirement for
general practices in England to offer patients aged 75 or over a named
accountable general practitioner, who should provide longitudinal continuity of
care within the general practice and be accountable for coordinating care to
meet the patient’s health and social care needs. In particular, the named
accountable general practitioner should ensure that patients receive all
appropriate services and work with relevant associated healthcare and social
care professionals to deliver a multidisciplinary care package [24,35]. The contract requires that the practice notify the patient of their
named accountable general practitioner, usually by letter, and make a reasonable
effort to accommodate patient preferences about the choice of general
practitioner. However, patients are not prevented from seeing any other general
practitioner in the practice [36]. The
2014/15 GMS contract changes led to a step change (discontinuity) in the
percentage of patients receiving a named accountable general practitioner, which
increases from around 5% to around 80% near age 75 (Table 1).

**Table 1 T1:** Preliminary analysis of data from Clinical Practice Research Datalink
showing that the requisite discontinuity exists in the data.

	Patients aged 70–74 (%)	Patients aged 75–79(%)

Notified of named accountable general practitioner	5420 (5%)	67,770 (80%)
Not notified of named accountable general practitioner	99,830 (95%)	17,161 (20%)
Total	105,250	84,931

*Note:* Based on preliminary analysis of Clinical
Practice Research Datalink data. Figures are illustrative as this
analysis was based on 2014 data and not all exclusion criteria were
applied.

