### Exposure variable and index dates

For reasons of patient confidentiality, Clinical Practice Research Datalink
contains year of birth rather than full date of birth. Therefore, age will be
calculated by subtracting the year of birth from 2014, and we will compare
patients whose age was in a small bandwidth (interval) above and below 75 years.
This bandwidth will be selected using standard cross-validation methods [31].

We will report the proportion of patients in each age group who received the
intended treatments. Since the policy ensures that the vast majority of patients
who are eligible for a named accountable general practitioner within 2014/15
will have received one by September 2014, treatment receipt will be based on the
presence of a recorded named accountable general practitioner within a 6-month
period (April 2014 to September 2014), using the Read code prescribed by the
General Medical Services contract (67DJ). Patients without a recorded named
accountable general practitioner by September 2014 will be regarded as untreated
patients, even if they received a named accountable general practitioner
subsequently.

All patients will be assigned an index date for the purposes of calculating
endpoints and covariates. For patients who are assigned a named accountable
general practitioner between April and September 2014, this will be the date at
which this was recorded. Patients who are not assigned a named accountable
general practitioner during this period will be randomly assigned an index date,
such that the distribution of index dates across months is the same as for those
patients who did receive one. Thus, all patients will have at least 6 months
follow-up within 2014/15, before the policy was extended to all patients
irrespective of age [39].

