### Study endpoints and covariates

Our primary endpoint will be the number of general practitioner contacts per head
over 6 months; this will include all appointment types (e.g. both surgery visits
and telephone calls). Secondary endpoints, also calculated over 6 months, will
be a measure of longitudinal continuity of care; the number of contacts with
general practitioners or practice nurses; numbers of referrals to specialist
care; and number of common diagnostic tests (e.g. blood pressure). There are
several measures of longitudinal continuity of care, which focus on the
concentration, dispersion, distribution or sequence of consultations [12,17]. The Usual Provider of Care index measures the proportion of
contacts with the general practitioner who is most commonly seen [17]. The Usual Provider of Care index is
widely used [11] and is more easily
interpreted than some of the other measures [12]. The Usual Provider of Care index was not chosen as the primary
endpoint, as this measure is only defined for the subgroup of study participants
with at least two general practitioner contacts during the study period. The
theory behind the intervention is such that a change to the number of general
practitioner contacts, referrals to specialist care or numbers of diagnostic
tests is more likely following an improvement to continuity of care. However, we
will analyse these endpoints regardless of the findings for the Usual Provider
of Care index, since it is theoretically possible that, for example, the letters
led to an increase in enquiries from patients without improvements to
continuity.

The following covariates will be calculated for all patients, using data recorded
prior to the index date: gender; ethnicity; socioeconomic score (attributed to
the patient according to their area of residence, and measured by deciles of the
Index of Multiple Deprivation 2010) [40];
number of long-term health conditions recorded prior to the index date; and
numbers of general practice contacts, referrals to specialist care, diagnostic
tests and hospital discharges in the 6 months prior to the index date. Long-term
conditions will be defined in accordance with the Quality and Out-comes
Framework. The data quality for the Quality and Outcomes Framework indicators is
enhanced as a result of these conditions forming part of the pay-for-performance
scheme for general practice [41].

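### The 6-month outcome window starts at the recording date for treated patients but at a random date for untreated ones, so any code entered at a GP contact can create a false step in contacts at 75

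*Protocol article*

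**What the plan says.** All of this is in the protocol article; no separate analysis plan was available.

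- **Role of the index date** (Exposure variable and index dates): "All patients will be assigned an index date for the purposes of calculating" endpoints and covariates.
- **Treated patients** (same section): for those given a named "general practitioner between April and September 2014, this will be the date at" which this was recorded, identified by Read code 67DJ.
- **Untreated patients** (same section): a patient without a named "general practitioner during this period will be randomly assigned an index date". The draw of these dates is constrained by calendar month only: it is made "such that the distribution of index dates across months is the same as for those" treated in that period.
- **Outcome** (Study endpoints and covariates): "Our primary endpoint will be the number of general practitioner contacts per head" over 6 months, with surgery visits and telephone calls both included.
- **Baseline** (same section): "The following covariates will be calculated for all patients, using data recorded" before the index date. The index day is thus outside the baseline window and, on the natural reading, inside the outcome window. The article does not say so outright.
- **Notification** (Reform to the general medical services contract in England): the practice tells the patient of the "named accountable general practitioner, usually by letter, and make a reasonable" effort to meet preferences. The share of codes entered during a consultation or call is not stated.
- **Take-up** (same section): receipt of a named general practitioner "increases from around 5% to around 80% near age 75 (Table 1").

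**The concern.** A random date has no link to the patient's contacts. A recording date may have one: if the code is typed in during a visit or call, the window opens on a contact by construction. Because recorded receipt jumps at 75, the share of windows opened by a contact jumps too, to 0.80s above the threshold against 0.05s below. Eligibility can then move the measured count without any change in care, which is what the exclusion condition of a fuzzy design rules out.

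Fitting the outcome models to all patients regardless of treatment does not help, since the outcome itself is measured differently according to treatment received. Matching by month balances season, not closeness to a contact.

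The primary estimate is at stake. So is the baseline check: prior 6-month contacts would be too low among patients coded at a contact. A counted index-day contact would also bring more treated patients up to the two contacts that the Usual Provider of Care index needs.

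**Working it through.** **Inputs.** Mean 5 contacts per 6 months, SD 6, target effect 5% × 5 = 0.25 (Required sample size). Take-up from Table 1. The share s of all 67DJ codes entered at a GP contact is an assumption shown as a range, taken as equal on both sides of 75.

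**The plan's own figures.** Table 1 reproduces: 5,420/105,250 = 5.1% and 67,770/84,931 = 79.8%, a jump of 0.746. The sample-size formula 2 × (1.960 + 1.282)² × 36 / 0.25² gives 12,105 per group, or 24,210 in all; the stated 24,212 in each group matches the total rather than the group size. That is a separate matter. Only the mean, SD and target are used here.

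**Model with no true effect.** Each patient has a constant rate λ per 6 months, gamma-distributed over patients, with Poisson contacts.
- Variance: 36 = 5 + 25/k, so k = 25/31 = 0.806.
- Probability of no contact in April to September: (0.806/5.806)^0.806 = 0.204. Probability of at least one: 0.796.
- Mean λ among those with none: 0.806/(0.806/5 + 1) = 0.694.
- A window from a random date contains λ contacts on average.

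Let a fraction f of treated patients be coded at a contact if they have one in April to September; all other codes fall on unrelated dates. Then s = 0.796f.

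**Code at the first contact, index day counted.** A patient with a contact has 1 + λ in the window, an excess of 1. A patient with none gets an unrelated date, and on average half of the window is known to be empty, an excess of -λ/2. Average: 0.796 - 0.204 × 0.694/2 = 0.796 - 0.071 = 0.725 per unit f, or 0.725/0.796 = 0.91 per unit s.

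**Code at an arbitrary contact, index day counted.** With n contacts in the period, the window holds (n + 1)/2 up to September and λ/2 after it, an excess of 1/2 + (n - λ)/2. With n = 0 the excess is -λ/2. Since n - λ averages zero over all patients, the result is 0.5 per unit s.

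**Index day dropped.** Subtract 1 per contact-coded patient: 0.91 - 1 = -0.09 per unit s (first contact) and 0.5 - 1 = -0.5 per unit s (arbitrary contact).

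**Effect on the fuzzy ratio.** The step in the count at 75 is 0.746 × c × s, where c is the coefficient above. Division by the treatment jump of 0.746 returns c × s per complier. The 0.91 is rounded to 0.9.

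| s | First contact, day counted | Arbitrary contact, day counted | First contact, day dropped | Arbitrary contact, day dropped |
|---|---|---|---|---|
| 0 | 0 | 0 | 0 | 0 |
| 10% | +0.09 | +0.05 | about 0 | -0.05 |
| 25% | +0.22 | +0.13 | about 0 | -0.13 |
| 50% | +0.45 | +0.25 | about 0 | -0.25 |

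With the day counted, the bias reaches 0.25 at s = 0.25/0.9 = 28% (first contact) or 0.25/0.5 = 50% (arbitrary contact).

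**Simulation check.** Simulating the same model gave +0.09, +0.22 and +0.45 for first-contact coding at s = 10%, 25% and 50%. For arbitrary-contact coding it gave +0.12 and +0.22 at s = 20% and 40% (simulation SE 0.03; formula 0.10 and 0.20), and -0.08 and -0.18 with the index day dropped.

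**Baseline contacts.** The 6 months before the index date mirror this: -0.91s or -0.5s per treated patient. The false step at 75 is 0.746 × 0.91s = 0.68s downwards (first contact) or 0.746 × 0.5s = 0.37s downwards (arbitrary contact), so roughly 0.4s to 0.7s.

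**The case against.** The strongest reply is that the whole bias rests on a quantity the article does not give, and what it does say points to a low value. Notification is mostly by letter, and the mechanism that Study endpoints and covariates foresees is that letters prompt enquiries. If practices entered codes in batches with the letters, s is near zero and so is the bias. This stands, and the point is therefore conditional.

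It is also fair that the direction is not fixed. A rise needs the index-day contact to be counted, and a condensed article may leave that rule to a fuller document. But dropping the day is not a safe repair, because under arbitrary-contact coding the bias then becomes negative. The unequal index rule itself is stated in the article, so it is not a detail left elsewhere.

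The plan also has a partial safeguard. Prior contacts are a listed covariate, and Statistical methods checks covariates for a step at 75. That check is graphical and might miss a step of 0.4s to 0.7s. If it did show one, the plan would count it against the design, although the index rule had caused it. The placebo thresholds cannot help, because take-up does not jump there.

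Three stronger readings are tempting and not supported:
- **That 80% of windows above 75 open on a contact.** Table 1 shows that 80% have a code; contact-triggered starts are 0.80s.
- **That the primary count is certainly biased upwards.** The sign depends on the index-day rule and on which contact carries the code.
- **That the false-positive rate is some definite high figure.** With the first-contact biases and linear trends (SE of the ratio 0.087 or 0.056 for 5 or 10 birth years a side), it would be about 18% to 97% for s between 10% and 25%. With quadratics (SE 0.177 or 0.097) it would be about 8% to 62%. The article fixes neither the polynomial order nor the bandwidth, these errors ignore clustering within practices, and Table 1 is labelled illustrative and covers only ages 70 to 79.

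**Conclusion.** The point holds in conditional form. The start of the outcome window depends on treatment received, and any link between code entry and GP contacts passes into the fuzzy ratio as a false effect that neither month matching nor the placebo thresholds remove.

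Its size is about +0.9s or +0.5s contacts per complier with the index day counted, and about zero or -0.5s without it, against a target of 0.25. These figures assume the plan's mean and SD, a contact rate that is constant over time for each patient, equal s on both sides of 75, and no clustering of follow-up visits after a contact; such clustering would add to the rise. Whether the bias matters in practice turns on s, which the study's own data can show.

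**What to change.** Set the window start by a rule that uses neither the patient's own code date nor treatment status. Two workable forms are:
- one date per practice, such as the median 67DJ recording date in that practice, applied to all its patients, treated or not; or
- a random date for every patient, treated or not, drawn from the same distribution.

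Apply the same rule to the secondary endpoints and the baseline counts. Leave the definition of treatment receipt as it is. Report the share of 67DJ codes entered on a GP contact day, which shows how exposed the present rule would have been. Add a common calendar window, 1 October 2014 to 31 March 2015, as a sensitivity analysis.

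The cost is rewording and reprogramming; no new data are needed. The downside is that follow-up will start somewhat before or after some patients' actual notification, which dilutes the effect a little. The October to March window is better kept as a sensitivity analysis than made the sole primary window: it misses early responses to the letters, and it lies after September, when patients classed as untreated may still receive a named general practitioner.

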### Study endpoints and covariates

Our primary endpoint will be the number of general practitioner contacts per head
over 6 months; this will include all appointment types (e.g. both surgery visits
and telephone calls). Secondary endpoints, also calculated over 6 months, will
be a measure of longitudinal continuity of care; the number of contacts with
general practitioners or practice nurses; numbers of referrals to specialist
care; and number of common diagnostic tests (e.g. blood pressure). There are
several measures of longitudinal continuity of care, which focus on the
concentration, dispersion, distribution or sequence of consultations [12,17]. The Usual Provider of Care index measures the proportion of
contacts with the general practitioner who is most commonly seen [17]. The Usual Provider of Care index is
widely used [11] and is more easily
interpreted than some of the other measures [12]. The Usual Provider of Care index was not chosen as the primary
endpoint, as this measure is only defined for the subgroup of study participants
with at least two general practitioner contacts during the study period. The
theory behind the intervention is such that a change to the number of general
practitioner contacts, referrals to specialist care or numbers of diagnostic
tests is more likely following an improvement to continuity of care. However, we
will analyse these endpoints regardless of the findings for the Usual Provider
of Care index, since it is theoretically possible that, for example, the letters
led to an increase in enquiries from patients without improvements to
continuity.

The following covariates will be calculated for all patients, using data recorded
prior to the index date: gender; ethnicity; socioeconomic score (attributed to
the patient according to their area of residence, and measured by deciles of the
Index of Multiple Deprivation 2010) [40];
number of long-term health conditions recorded prior to the index date; and
numbers of general practice contacts, referrals to specialist care, diagnostic
tests and hospital discharges in the 6 months prior to the index date. Long-term
conditions will be defined in accordance with the Quality and Out-comes
Framework. The data quality for the Quality and Outcomes Framework indicators is
enhanced as a result of these conditions forming part of the pay-for-performance
scheme for general practice [41].

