## Introduction

There has been a concerted effort in recent years to promote more integrated care in
England [1,2,3]. Integrated care is a term
often used to describe services that are coordinated around the patient and based
around their needs [1,2]. Continuity of care is an important part of this vision, and
patient satisfaction is strongly linked to the ability to see a doctor with whom the
patient has a personal relationship [4].
However, due to increased specialisation within primary care and the end of
‘personal registration’ with a particular general practitioner in the
last 10 years, there is concern that it is becoming more difficult for patients to
see their preferred general practitioner [5,6]. In England, 54% of patients
have a general practitioner they preferred to see, and this proportion is higher
among patients aged 75 and over, at 75% [7,8]. However, among adults with a
preferred general practitioner, 31% saw them only some of the time and 8% never or
almost never saw them in 2013/14 [9].

The term continuity of care has been used in a variety of ways and can encompass many
different ideas [10,11,12,13,14].
One model distinguishes between three related but distinct concepts: longitudinal
continuity of care with as few doctors or healthcare professionals as possible;
coordinated care, with good communication between professionals and a consistent
approach to the management of health needs; and the subjective experience of a
caring relationship [12]. There is evidence
that the various aspects are associated with positive effects on a range of
outcomes, including more appropriate prescribing and higher quality of life [14]. In particular, longitudinal continuity may
be an important element in interventions to reduce emergency department visits and
unscheduled hospital admissions [14,15,16].
Subjective continuity of care is strongly linked to patient satisfaction [4,10,17], which in turn may be a predictor of
compliance with following recommended treatments [14,18]. Although one study
reported that patients with a personal relationship with their general practitioner
experienced fewer referrals to specialist care than other patients [19], a retrospective cohort study suggested
more complex associations between longitudinal continuity and time to referrals and
diagnoses for certain cancers [20].

Many evaluative studies of the effect of interventions aimed at greater continuity of

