## Statistical methods

Our initial analysis (Table 1) suggests that
the proportion of patients receiving a named accountable general practitioner is
discontinuous at the threshold, but this will be confirmed on receipt of the data.
We will also confirm that, although we would expect a trend in certain covariates
across age, there are no discontinuities in these covariates at age 75. This
comparison will be done graphically and include all patients, regardless of actual
treatment assignment. We do not expect such discontinuities to occur, but if they do
exist, this would lead us to question the validity of our study design.

As mentioned previously, the proportion of patients receiving a named accountable
general practitioner is unlikely to jump from 0 to 100% at age 75. It will therefore
be appropriate to apply a fuzzy regression discontinuity design [31], by fitting four regression models. Two
models will relate the outcome to a polynomial function of age: one model will be
fitted for people whose age lies within the bandwidth below the threshold and the
other model for people within the bandwidth above the threshold. The final two
models have treatment assignment as their dependent variable rather than outcome.
All models will use ordinary least squares regression and include patients
irrespective of their actual treatment assignment. We will calculate the estimated
treatment effect as the difference between the predictions of the two outcome models
at age 75, divided by the difference between the predictions of the two treatment
models at age 75.

The analysis will have regard to the rounded nature of the running variable (i.e.
age), resulting from the use of year of birth rather than full date of birth. This
will exclude the use of very small bandwidths, and so we will use a larger interval
spanning several years and model any trend in the endpoints by age using parametric
approaches based on polynomial functions [42,43]. In the absence of
information on full date of birth, it will not be possible to establish for a given
patient born in 1939 what date they turned 75, and therefore which side of the
threshold the patient is at the index date. We will remove the risk of
misclassification by excluding all patients born in 1939 when fitting the regression
models and making a small extrapolation around age 75 [42]. A final consideration is that, when the running variable
is only observed at discrete points, discretisation bias can occur because a change

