in slope close to the cut-off might be mistaken for a treatment effect when in fact
it is due to the ‘natural’ change in outcomes with age. We will correct
for this bias using a method that is based on the moments of the age distribution
[42].

We will conduct a series of additional specification tests to check the validity of
the study design [31]. First, we will repeat
the estimation procedure at non-discontinuity points, to confirm a treatment effect
of zero. Second, we will confirm that the estimated treatment effect is not
sensitive to the choice of bandwidth or order of polynomial. Third, we will repeat
the analysis when including covariates in the regression models. Although it is not
necessary to include covariates in regression discontinuity analyses, including them
may improve precision [37,42].

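### The continuity index has no lagged counterpart among the covariates, so no planned check would reveal a step in continuity at age 75 that predates the policy

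*Protocol article*

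**What the plan says.** Under Study endpoints and covariates, the primary endpoint is GP contacts over 6 months. The first secondary endpoint is to "be a measure of longitudinal continuity of care; the number of contacts with" GPs or practice nurses, followed by referrals and diagnostic tests. Continuity is measured by the Usual Provider of Care index, which needs at least two GP contacts. The last paragraph of the Introduction states the aim as assessing change in longitudinal continuity.

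The covariates form a definite list: "The following covariates will be calculated for all patients, using data recorded" before the index date. It comprises gender, ethnicity, deprivation, number of long-term conditions, and "numbers of general practice contacts, referrals to specialist care, diagnostic" "tests and hospital discharges in the 6 months prior to the index date". No continuity measure is on it.

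Statistical methods uses the list in two ways. The validity check is that "there are no discontinuities in these covariates at age 75", judged graphically. A later sensitivity analysis repeats the estimation with covariates included. A separate placebo step repeats "the estimation procedure at non-discontinuity points, to confirm a treatment effect" of zero. The article also plans sensitivity to bandwidth and polynomial order, and a correction for discretisation bias.

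**The concern.** The design assumes that, without the policy, outcomes vary smoothly through age 75. The most direct evidence for a given outcome is that the same outcome, measured before the policy, shows no step there. The plan provides something close to this for contacts, referrals and tests, and even includes hospital discharges, which are not an endpoint. It does not provide it for the outcome nearest to the stated aim.

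Suppose continuity already stepped up at 75, for example because some practices gave patients a regular doctor from that age. The other covariates need not show it, and the fuzzy estimate would credit it to named GPs. A smaller loss is that prior continuity is probably a useful predictor of later continuity, and the adjusted analysis cannot use it.

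**Working it through.** The article gives no figure for the continuity index, so there is none to reproduce. The check is mainly a comparison of lists.

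**Endpoints against the covariate list**

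| Endpoint | 6-month pre-index counterpart |
|---|---|
| GP contacts | general practice contacts |
| GP or nurse contacts | general practice contacts |
| Referrals | referrals |
| Diagnostic tests | diagnostic tests |
| Usual Provider of Care index | none |

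**What each planned check can see for continuity**

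- Covariate check at 75: limited to the listed covariates, so prior continuity is not examined.
- Placebo estimates: run at ages other than 75, so they say nothing about a step at 75.
- Discretisation correction, bandwidth and polynomial sensitivity: these address a change in slope near 75. A genuine step at 75 need not disappear under any of them.
- Covariate-adjusted repeat: adjusts for prior contacts, long-term conditions, deprivation and the rest, but not prior continuity.

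What remains uncovered is a step in continuity at 75 that predates the policy.

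**Pre-index is not pre-policy.** Index dates run from April to September 2014. A 6-month window before a September 2014 date starts in March 2014 and lies mostly within the policy period. A clean continuity check therefore needs a fixed period ending before April 2014.

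**How a pre-existing step would enter the estimate.** The estimator is the outcome jump divided by the treatment jump. Table 1 gives about 80% − 5% = 75 points, from illustrative data in 5-year age bands. A step of size s that persists in full adds s/0.75 = 1.33s. For an arbitrary s of 0.02 this is 0.02/0.75 = 0.027. With a carry-over of only 0.3 to 0.5 it is 0.02 × 0.3/0.75 = 0.008 to 0.02 × 0.5/0.75 = 0.013. Only the divisor comes from the article.

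**Precision forgone.** Adjusting for a baseline value with pre/post correlation r multiplies the standard error by √(1 − r²). The article gives no r, so I assume 0.3 to 0.5:

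- r = 0.3: √0.91 = 0.954, about 5% smaller.
- r = 0.5: √0.75 = 0.866, about 13% smaller.

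These are upper limits for each r, because the baseline index is undefined for some analysed patients.

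**Availability of a baseline index.** Take the mean of 5 and SD of 6 contacts per 6 months from Required sample size, and assume a negative binomial distribution. The dispersion parameter is 25/(36 − 5) = 0.806, and about 66% of patients have at least two contacts in 6 months. At least two contacts in both of two such periods occur in about 43% if the periods are independent, and about 56% if each patient's underlying rate is fully shared. Among patients in the continuity analysis, a 6-month baseline index would therefore exist for about 66% (0.429/0.655) to 86% (0.564/0.655).

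**The case against.** The strongest case against is that this is an omission from a condensed article. Covariates are optional in a regression discontinuity design, and the article says so. Covariate checks are offered only as an example of validation. The list is of variables calculated for every patient, whereas the index exists only for those with two or more contacts. Continuity is one of several secondary endpoints.

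Part of this stands. The missing adjustment is not a bias, and the primary endpoint is untouched. The list, however, is stated as definite and covers the other outcomes, so it is more than detail left to a fuller document. The restriction to two contacts is no obstacle, because the endpoint carries the same restriction.

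A reader might infer three stronger things, and the article supports none of them:

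- *That the continuity endpoint has no baseline adjustment at all.* The adjusted repeat still uses the other listed covariates. Only prior continuity is missing.
- *That a bend in continuity near 75 would pass unnoticed.* Statistical methods names a change in slope near the cut-off as a risk, plans a correction for it, and adds bandwidth and polynomial sensitivity runs.
- *That the Introduction shows continuity changing at 75.* It reports that 54% of patients have a preferred GP and that the share is higher "among patients aged 75 and over, at 75" per cent. This compares all patients with everyone aged 75 and over, on preference and not on the index. It fits a smooth age gradient and does not show a step.

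**Conclusion.** The point holds in a limited form. Continuity lacks the lagged check at 75 that contacts, referrals and tests receive, and no other planned analysis would detect a pre-policy step there. Whether such a step exists is unknown. The article also gives no meaningful difference for the index, so the illustrative bias figures cannot be judged large or small. The forgone precision is at most about 5% to 13% of the standard error under an assumed correlation of 0.3 to 0.5. The main value of the change is the validity check, with precision second. It is worth making because continuity is the stated aim and the cost is small. It is not an error that invalidates the design.

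**What to change.** Two additions:

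- **Placebo at age 75 before the policy.** Run the same estimation on the Usual Provider of Care index in a fixed period ending before April 2014, among patients with at least two GP contacts in that period. Redefine age and the excluded birth year for that earlier year, so that the cut-off is age 75 at that time. For a period within calendar 2013, age is 2013 minus birth year and those born in 1938 (2013 − 75) are left out. Patients born in 1937 or earlier are then all at least 75, and those born in 1939 or later are all under 75. Read the jump in the index itself, since there was no treatment jump to divide by.
- **Baseline continuity as a covariate.** Derive the index over one fixed pre-policy period for all patients, for example the 12 months to 31 March 2014, with an indicator for fewer than two contacts. Include it in the check for discontinuities at 75 and in the covariate-adjusted sensitivity analysis of the continuity endpoint.

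The cost is one derived variable, a missing-category term and one extra placebo run. The extract must reach back to the chosen period. The existing covariates already need data from about October 2013, which is 6 months before the earliest index date.
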